### Study organization

The trial is investigator initiated and controlled by a steering committee including anesthetists and intensive care physicians, all with solid research experience. The executive committee comprises the study’s principal investigator and the principal investigators of the investigating centers that approved the final trial design and protocol issued to the clinical sites.

An independent data and safety monitoring board (DSMB) monitors patient safety and reviews safety issues as the study progresses. All serious adverse events and all unexpected and related or possibly related adverse events are reported to the appointed international manager for serious adverse events, who assesses the events and reports this information to the DSMB.

Data management is performed by the Centre for Clinical Studies at Dresden University of Technology, Germany, using study software MACRO 3.0. The data are proven by programmed range checks, validity checks and consistency checks. In addition, there is a manual and visual check of the data for medicinal plausibility according to good clinical practice guidelines. Intervention period data are checked periodically to monitor adherence to the protocol, thereby giving feedback to staff. Trial updates are published on the trial website.

## Discussion

To our knowledge, the present study protocol is the first to address the effects of variable PSV on the duration of weaning in intensive care unit patients. This study is the first international multicenter trial on variable ventilation.

There is a considerable body of experimental evidence showing that variable mechanical ventilation is beneficial in terms of lung function and damage, compared to non-variable mechanical ventilation. Variable controlled ventilation has been shown to improve gas exchange and lung mechanics in experimental models of the acute respiratory distress syndrome (ARDS) in small [15-17] and large animals [11,12,18,19]. Also, variable controlled mechanical ventilation has the potential to reduce histologic lung damage and pulmonary inflammation [18]. The exact mechanisms behind such effects have not been elucidated so far, but release of a lung surfactant [16,20], lung recruitment [21,22] and stochastic resonance [15,19,23] have been suggested. In addition, one randomized controlled trial suggested that intraoperative variable controlled mechanical ventilation improves oxygenation and respiratory system compliance in patients submitted for surgical repair of an aortic aneurysm [24]. However, clinical outcome variables were not reported for that study. Currently, in the PROVAR trial (protective variable ventilation for open abdominal surgery; ClinicalTrials.gov identifier: NCT01683578), our group is investigating whether variable volume controlled ventilation is able to reduce the incidence of postoperative pulmonary complications. Nevertheless, that trial is being conducted in the operation room only. Thus, patients are under general anesthesia and muscle paralysis. In addition, the duration of the intervention is limited to three to ten hours.

Variable PSV is a new mode of mechanical ventilation able to combine variable ventilation with assisted mechanical ventilation. Experimental studies on models of ARDS have demonstrated that variable PSV improves gas, reduces the elastance of the respiratory system and the inspiratory effort as well as respiratory drive, compared to non-variable modes of assisted ventilation. Furthermore, variable PSV reduced lung inflammation and damage in experimental ARDS compared to protective controlled mechanical ventilation [12,18].

The ViPS trial will broaden our knowledge of the impact of variable PSV on important clinical outcome variables in a mixed ICU population. The inclusion and exclusion criteria have been carefully designed to include a large number of patients, regardless of their co-morbidities, while taking safety issues into account. Thereby, the use of variable PSV, which has been evaluated only for hypoxemic lung failure, will be expanded to other patient groups. The protocol described here represents a consensus among centers and investigators with considerable experience in weaning patients from mechanical ventilation. The interventions are an agreement between several weaning strategies conducted in the participating centers, while the variable PSV settings have been carefully derived from experimental knowledge combined with clinical experience. Therefore, compliance of the participating centers to the protocol is likely.

The ViPS trial protocol has limitations that must be addressed. First, the entry criteria allow for patients with large differences in weaning duration, ranging from hours to days. These differences have been considered in the sample size calculation. Second, patients who fail to wean may be transferred to weaning centers, resulting in them being lost to follow-up and, consequently, causing a reduction in study power. Nevertheless, the dropout rates considered in the sample size calculation represent a worst case scenario for the participating centers. Third, the protocol cannot be conducted in a blinded fashion, which can favor bias. To minimize this effect, we defined a tight protocol where intervention steps mandate handling until the primary endpoint is achieved. Fourth, even though the protocol interventions represent a consensus among centers, local differences in weaning experience and standards may still affect the results of this trial. Fifth, the use of non-invasive ventilation following extubation could introduce bias in terms of a reduction of weaning time, but this effect should not affect the comparative performance of variable PSV, since it is also allowed in the control group.

In conclusion, ViPS is the first randomized controlled trial that compares variable with non-variable PSV with respect to the duration of weaning from mechanical ventilation in a mixed ICU population. This trial may also clarify how and why variable PSV improves lung functional variables, and reduces the respiratory drive.

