### Baseline data

After screening the following demographic characteristics will be documented: patient’s age, sex, height, weight, predicted body weight, date and type of hospital admission, date and type of surgery, date of ICU admission and time of mechanical ventilation. If a patient meets the inclusion and exclusion criteria we record the following: acute physiology and chronic health evaluation (APACHE) II score and sequential organ failure assessment (SOFA) score. Before and after the pre-inclusion test we record the following: date and time of pre-inclusion test, ventilation mode before and after pre-inclusion test, minute ventilation, respiratory rate, tidal volume, peak airway pressure, mean airway pressure, PEEP, FiO_2_, PaO_2_, arterial partial pressure of carbon dioxide (PaCO_2_) and pH.

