### Study endpoints

The primary endpoint is weaning time, defined as the time from randomization to successful extubation.

Secondary endpoints are: total time of mechanical ventilation; time from randomization to first extubation; time from randomization to fulfillment of extubation criteria; time between fulfillment of extubation criteria and extubation; ICU length of stay, in-hospital length of stay; ICU and in-hospital-mortality; mortality at day 90 and 6 months; PaO_2_/FiO_2_; PaCO_2_; total minutes of ventilation; mean tidal volume; mean pressure support; mean airway pressure; mean peak inspiratory pressure; inspiratory airway occlusion pressure at 100 ms; visual analogue scale for breathing comfort; cumulative amount of sedative and analgesic drugs; SOFA score; re-intubation rate; use of non-invasive ventilation; post-extubation duration of NIV; ventilator-free days (28 days); number of changes in mean pressure support by ICU personnel; coefficients of variation of tidal volume and pressure support; respiratory rate, and inspiratory and expiratory times.

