### Statistical considerations

#### Sample size calculation

The sample size calculation (GPower software version 3.1.3, University of Düsseldorf, Germany) was based on the Wilcoxon–Mann–Whitney test (two groups, two tailed). The calculation was based on the expectation that the primary endpoint variable (time from randomization to successful extubation) would show a difference of 2 days between the two treatment groups. Based on the study by Lellouche *et al*. [14] the standard deviation (SD) was estimated as 5 days for both groups, yielding an effect size (*d*) of 0.4. Accordingly, 104 patients per group would allow the detection of differences between the groups with a power of 80% and a type one error rate of 5%. Assuming that 10 dropouts per group may occur, 228 patients in total are necessary.

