#### Statistical analysis

The descriptive analysis will include the mean and standard deviation for normally distributed variables. Variables that are not normally distributed will be expressed by their medians and interquartile ranges. Categorical variables will be expressed as *n* (%). Differences in the primary endpoint variable, time from randomization to successful extubation between the two treatment groups, will be analyzed by a Wilcoxon–Mann–Whitney test.

To decide on the proper comparison method for the exploratory analysis of the secondary endpoints, we will test whether the variables are normally distributed. Student’s *t*-test will be used to test groups of independent continuous normally distributed variables. The Mann–Whitney *U* test will be used for continuous variables that are not normally distributed. Categorical variables will be compared with the chi-square test or Fisher’s exact test. Paired data will be analyzed using Student’s *t*-test for continuous normally distributed variables, the Wilcoxon test for continuous variables that are not normally distributed and the McNemar or Bowker test, as appropriate, for categorical variables.

Kaplan–Meier survival curves will be computed to evaluate differences in overall survival. Survival curves will be compared by a log-rank test and multivariable analysis will be accomplished by the Cox regression model.

If any patients are lost to follow-up or withdraw consent for the trial, the reasons will be reported. The intention-to-treat (ITT) analysis and per protocol (PP) analysis will be conducted to test whether the result of this trial is reliable. Missing data will be handled by means of the last-observation-carried-forward method. For the intention-to-treat analysis, data will be processed for all trial patients in the groups to which they were randomized, regardless of whether they received or adhered to the allocated intervention.

It is assumed that the majority of patients in the two triage arms will receive the appropriate study intervention. The per protocol analysis will be performed as a secondary analysis if there are sufficient patients in the triage arms who do not receive study therapy or are lost to outcome assessment. Data from participants who do not violate the treatment protocols will be included in the per-protocol analysis.

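### The primary rank test is valid and adequately powered, but it uses neither centre nor the baseline values recorded before randomisation, so it gives up some efficiency

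*Protocol article*

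**What the plan says.** **Endpoint and test.** Under Study endpoints: "The primary endpoint is weaning time, defined as the time from randomization to successful extubation". Under Statistical analysis, the difference between the arms "will be analyzed by a Wilcoxon–Mann–Whitney test". No centre or covariate term is given. The sample size calculation rests on the same test, two-sided.

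**Multivariable modelling.** The only such model is in the paragraph on overall survival: "multivariable analysis will be accomplished by the Cox regression model". Nothing ties it to weaning time.

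**Baseline data.** For eligible patients the Baseline data section records "acute physiology and chronic health evaluation (APACHE) II score and sequential organ failure assessment (SOFA) score". It also records time on the ventilator and, before and after the pre-inclusion test, PEEP, FiO2, PaO2, PaCO2 and pH. The Pre-inclusion test section allows randomisation only once that test is passed.

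**Randomisation and limitations.** The Randomization section blocks the sequence by centre. The Discussion's first limitation is that "the entry criteria allow for patients with large differences in weaning duration, ranging from hours to days", and it says the sample size calculation took this into account. The fourth limitation accepts that differences between centres in weaning practice may affect the results.

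**The concern.** The protocol names two sources of variation in the primary endpoint, patients and centres. It holds data on both at randomisation, yet its primary test uses neither. Its answer on patient heterogeneity is the sample size, where the spread enters as an SD of 5 days. That sizes the trial for the noise but does not remove the part that recorded data could explain.

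The document itself gives a reason to think that some of these values are prognostic. Patients may enter with PaO2/FiO2 as low as 150 mmHg and PEEP as high as 16 cmH2O. The extubation criteria ask for PaO2/FiO2 of at least 200 mmHg (150 in chronic obstructive pulmonary disease) and PEEP of at most 8 cmH2O. A patient who enters at the limits has further to go on both than one who already meets them, so baseline oxygenation and PEEP measure a distance to the endpoint.

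At stake is precision. The size leaves little slack on its own inputs, and the Discussion expects transfers to weaning centres to cost some power.

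**Working it through.** **Inputs from the Sample size calculation section.** The difference is 2 days (the endpoint "would show a difference of 2 days between the two treatment groups") and the SD is 5 days in both groups, so d = 2/5 = 0.4. The test is two-sided at 5% with 80% power. The stated size is 104 per group plus 10 dropouts per group, 228 in total.

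**Step 1: reproduce the plan's figure.** Use noncentral-t power, with n scaled by the asymptotic relative efficiency of the Wilcoxon test under a normal parent, 3/π.
- Effective n per group: 104 × 3/π = 99.3.
- Noncentrality: 0.4 × √(99.3/2) = 2.82.
- Power: 80.1%. With 103 per group it is 79.7%, so 104 is the smallest size that reaches 80%.
- Total: 2 × (104 + 10) = 228.

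Both stated figures reproduce.

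**Step 2: what adjustment could add.** Let R² be the share of rank variance explained by the baseline values. The document gives no R², so 0.05 to 0.20 is assumed. The residual SD is 5 × √(1 − R²), and the noncentrality becomes 2.82 / √(1 − R²). The n that keeps 80% power is about 104 × (1 − R²), rounded up.

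| R² (assumed) | Residual SD (days) | Noncentrality | Power at 104 per group | n per group for 80% |
|---|---|---|---|---|
| 0 | 5.00 | 2.82 | 80.1% | 104 |
| 0.05 | 4.87 | 2.89 | 82.1% | 99 |
| 0.10 | 4.74 | 2.97 | 84.1% | 94 |
| 0.20 | 4.47 | 3.15 | 88.0% | 84 |

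**Step 3: check by simulation.** There were 4000 runs per setting, with 104 per group, normal outcomes with SD 5, a 2-day shift and one covariate. R² was set on the outcome scale. The unadjusted test was compared with a rank-ANCOVA (Quade) test.
- R² 0.10: 79.7% unadjusted, 83.0% adjusted.
- R² 0.20: 79.6% unadjusted, 87.6% adjusted.
- With no true difference, type I error was 4.5% to 5.2% for both tests over R² of 0.10 to 0.30.

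The simulation agrees with the formula to within about 1 point at these two settings.

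**Not computed.** No figure is given for stratifying by centre, because the document states neither the number of centres nor the variation between them. The table covers the baseline values only.

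**The case against.** The case for leaving the plan alone is substantial.

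- **The planned test is sound.** An unadjusted rank test is valid in a randomised trial, it is the test used for the sample size, and that sample size is right on its inputs. This stands in full.
- **The heterogeneity was answered.** When an unadjusted test is powered, the marginal SD is where between-patient spread belongs, so the Discussion's reply is consistent with the calculation. This stands. A reader might infer that the trial is underpowered because of heterogeneity, but the document's figures do not support that.
- **The predictive value is unknown.** A reader might infer that the recorded scores predict weaning time strongly. The document reports no correlation for any of them. The predictors that its Background discusses are variability of tidal volume and of respiratory rate, which are not on the baseline list. The pre-inclusion test also narrows the range of oxygenation and other physiology at entry. So the values can be called plausibly prognostic and no more.
- **Chance imbalance.** A reader might also infer that imbalance in severity between the arms goes uncorrected. Under randomisation the 5% error rate already allows for it, so it is not a defect.
- **The analysis plan may cover this.** A supportive adjusted analysis could well be in the unseen analysis plan, and its absence here is no fault. But the primary test is fixed in this text, so that choice can be reviewed.

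What remains is efficiency, together with the mismatch between randomising within centre and analysing without it.

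**Conclusion.** This is a minor point: a better method is available at almost no cost, and nothing in the plan is wrong. The planned test keeps its type I error and reaches its stated power. Adjusting for recorded baseline values would add about 2, 4 or 8 points of power at 104 per group if they explained 5%, 10% or 20% of the rank variance. At the same 80% power, that is equivalent to 5, 10 or 20 fewer patients per group (104 less 99, 94 or 84).

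The size rests on the assumed R², on normal outcomes and, in the simulation, on a single covariate. With skewed or censored weaning times the gain may be smaller or larger. That there is something to gain is plausible from the protocol's own entry and extubation limits and from its remark on centre differences, but the document does not demonstrate it.

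**What to change.** Before any outcome data are seen, pre-specify as the primary analysis a rank-based ANCOVA of the same endpoint, stratified by centre. Adjust it for a short fixed list of values already recorded before randomisation, for example APACHE II, SOFA, PaO2/FiO2 at the pre-inclusion test and prior ventilation time. State for the blood-gas value whether the reading before or after the pre-inclusion test is used. Keep the unadjusted Wilcoxon–Mann–Whitney test as a sensitivity analysis. The endpoint definition does not change.

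The cost is wording in the protocol and analysis plan, with no new data or visits. There are three downsides: a model to pre-specify, slightly more complex reporting, and a primary test that no longer matches the sample-size test exactly. The size of 104 per group need not change. It was set without any gain from adjustment, so it stays conservative as long as the covariates explain some of the variation.

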## Abbreviations

APACHE: Acute physiology and chronic health evaluation (score); ARDS: Acute respiratory distress syndrome; BPS: Behavioral pain scale; CONSORT: Consolidated standards of reporting trials; CPAP: Continuous positive airway pressure; CRF: Case report form; DSMB: Data and safety monitoring board; FiO2: Inspiratory oxygen fraction; ITT: intention-to-treat; ICU: Intensive care unit; NIV: Non-invasive ventilation; P0.1: Airway inspiratory occlusion pressure at 100 ms; PaO2: Arterial partial pressure of oxygen; PaCO2: Arterial partial pressure of carbon dioxide; PEEP: Positive end-expiratory pressure; PP: Per protocol; PSV: Pressure support ventilation; RASS: Richmond agitation and sedation scale; RR: Respiratory rate; SaO2: Oxygen saturation; SOFA: Sequential organ failure assessment (score); SSL: Secure sockets layer; VAS: Visual analogue scale; ViPS: Variable pressure support trial; VT: Tidal volume.
